## Abstract

**Background:**

Lateral lymph node (LLN) metastasis is a major cause of local recurrence of advanced rectal cancer. Although there is much controversy between Western and Eastern countries on whether lateral pelvic lymph node dissection (LLND) or neoadjuvant chemo-radiation (nCRT) is preferable for the treatment of LLN metastases, existing retrospective cohorts mainly focus on all middle/low advanced rectal cancer patients, not the specific individuals with suspicion of LLN metastases. The aim of this trial is to assess the efficacy and safety of LLND for rectal cancer patients with suspicion of LLN metastases.

**Methods:**

This prospective, multicenter, randomized controlled, single-blinded, phase III trial is designed to enroll 512 eligible patients with advanced rectal cancer and preoperative enlarged lateral lymph nodes. The population will be randomly assigned into the solely total mesorectal excision (TME) group or the TME + LLND group after eligible selection. The primary outcomes are to be 3-year local recurrence rate and 3-year disease-free survival, and the secondary outcomes include 3-year overall survival, 1-year sexual and urinary function, and perioperative outcomes.

**Discussion:**

This is the first randomized trial to investigate the efficacy and safety of LLND for advanced low rectal cancer patients with suspicion of LLN metastases; the result is expected to provide new evidence for the treatment of LLN where there is suspicion of metastases in advanced rectal cancer patients.

**Trial registration:**

This trial was registered at ClinicalTrials.gov (identifier NCT02614157) Registered on 24 November 2015.

## Background

Rectal cancer is the third most common cancer and the fourth leading cause of cancer-related deaths worldwide [1]. Local recurrence of middle/low rectal cancer is not only a poor prognostic factor but also a threat of a terrible quality of life. Although universal usage of neoadjuvant chemo-radiation (nCRT) and total mesorectal excision (TME) have decreased local recurrence rates to 5–10%, the ratio of local recurrence has occupied almost 30% of total metastases and recurrence incidences, which heavily limits the therapeutic effect for advanced rectal cancer [2]. Increasing evidence has demonstrated that lateral pelvic lymph node (LLN) metastasis is a major cause of local recurrence of advanced rectal cancer [3]. At the time of diagnosis, 10–25% of patients with advanced rectal cancer have synchronous LLN metastases, which consequently lead to local recurrence and poor overall survival [4, 5].

Regarding the treatment strategy for LLN metastases, there is much controversy between Western and Eastern countries on whether lateral pelvic lymph node dissection (LLND) [6–10] or nCRT [11, 12] is the best treatment option. Eastern countries, especially Japan, favor LLND following TME for the following reasons: (1) the incidence of LLN metastases reaches as high as 10–25%, and 27% of rectal cancer patients who undergo TME solely (without LLND) would develop local recurrence [13–16], (2) the efficacy of LLND equals that of resection of local lymph node metastases. A large cohort of 11,567 cases from Japan demonstrates that resection of metastatic iliac lymph nodes does not show any differences between TME in patients with clinical stage TxN2aM0, and resection of obturator and external iliac lymph nodes favors that of liver metastasis [11], and (3) Japanese guidelines for the treatment of colorectal cancer in 2014 still recommend that patients with stages II/III rectal cancer below the peritoneal reflection undergo regular TME + LLND [17].

On the contrary, Western countries favor nCRT and TME for LLN metastases, holding that: (1) the rate of LLN metastases is relatively low, and LLN metastases are regarded as systemic metastases, (2) LLND involves longer operative time, higher postoperative complications, and results in a poorer quality of life. Therefore, American NCCN and European ESMO guidelines recommend single TME for rectal cancer but, if necessary, LLDN is added when LLN indeed show evidence of metastases.

Despite this, existing retrospective cohorts mainly focus on all middle/low advanced rectal cancer patients, not the specific individuals with suspicion of LLN metastases. And those results indicate almost no differences in local recurrence and overall survival, except for longer operation time, more blood loss, and more perioperative complications for LLND [7–9, 18]. A Korean report enrolled 900 advanced rectal cancer patients with preoperative swollen LLNs, which showed that the recurrence rate was associated with the diameter of the LLNs [16]. However, there is no strict prospective randomized controlled study on the comparison of TME + LLND and TME for low rectal cancer with suspicion of LLN metastases after nCRT. Thus, the objective of this study is to assess the efficacy and safety of LLND for low rectal cancer patients with suspicion of LLN metastases (TME + LLND versus TME). Furthermore, the risk factors (such as radiologic factors, pathologic factors, and serum protein) to predict local recurrence and overall survival will be further investigated.

## Methods

### Study design

This is a prospective, multicenter, randomized controlled, single-blinded, phase III trial in which patients will be randomly assigned into two parallel comparison groups (the TME + LLND group and the TME group). The flow diagram of this trial is shown in Fig. 1. Our trial began in May 2016 in the West China Hospital of Sichuan University and is expected to end in 2022.

**Fig. 1 Fig1:**
[figure not shown]
Example template of recommended content for the schedule of enrollment, interventions, and assessments

### Ethics

This trial protocol has been approved by the Ethics Committee of West China Hospital of Sichuan University on 13 May 2016 with protocol number 89, and is registered at ClinicalTrials.gov (identifier NCT02614157). Written informed consent will be obtained from every patient.

### Study population

The inclusion and exclusion criteria of our trial are shown in Table 1. All eligible patients will strictly comply with the criteria.

**Table 1 Tab1:** The inclusion and exclusion criteria

Inclusion criteria:
•Age (years): 18–75
•Histologically confirmed rectal cancer
•Clinical stage: cTxN1-2M0 or cT3-4N0M0
•Suspicion of LLN metastasis: short-axis diameter of lateral lymph nodes (LLN) >5 mm; short diameter of common iliac or external iliac lymph nodes >6 mm [16, 24, 25]
•No extramesorectal lymph node swelling (short-axis diameter <10 mm)
•No invasion of other organs
•Performance Status (PS): 0, 1
•No past history of chemotherapy, pelvic surgery, or radiation
•Written informed consent operative criteria:
•Mesorectal excision is performed
•Operative findings:
Main lesion of the tumor is located at the rectum
Lower tumor margin is below the peritoneal reflection
Stage R0 after resection
Exclusion criteria:
•High rectal cancer: lower tumor margin is above the peritoneal reflection
•Multiple-cancer patients
•Pregnant patients
•Patients with psychological disorder
•Steroid administration
•Cardiac infarction within previous 6 months
•Severe pulmonary emphysema and/or pulmonary fibrosis
•Physician’s decision to exclude
•Patients with confirmed LLN metastasis: short-axis diameter of LLN >10 mm and a lymph node with an irregular edge, heterogeneous signal, or obvious enlargement and after nCRT has been completed, lymph node enlarges more than 30%
•Emergency surgery
•Patients with coagulopathies

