### Randomization and blinding

All eligible participants meeting the inclusion criteria will be randomly allocated into either the TME + LLND group or the TME group. Based on one previous study, randomization is performed using a computer-generated, blocked randomization sequence with a block size of 4 at a 1:1 ratio [19]. The patients will be informed about the treatment details upon admission the day before surgery. Owing to the specificity and ethics, this trial allows the participants, the surgeon, and the investigators to be aware of the whole assignment.

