### Intervention

After randomization, all participants will firstly receive a cycle of 5-fluorouracil with oxaliplatin therapy (FOLFOX) or capecitabine (Xeloda) with oxaliplatin therapy (XELOX). Subsequently, radiotherapy with 50.4 Gy is administered in 28 separate doses. Next, three cycles of FOLFOX or XELOX will be continued. About 3 to 4 weeks later, patients allocated to the TME group will undergo standard TME surgery solely, while patients allocated to the TME + LLND group will undergo standard TME surgery plus LLND. The extent of LLND includes bilateral LLND (lymph node groups 263P, 263D, and 283). If the short-axis diameter of the external iliac or common iliac lymph nodes is beyond 6 mm, lymph node groups 293, 273, and 280 will be dissected. Unilateral LLND will be done only when the center of the rectal tumor is limited to a single side (not beyond the midline) and the contralateral lymph nodes are not enlarged. Adjuvant chemotherapy, consistent with the preoperative scheme in every patient, will be continued until reaching eight cycles.

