### Sample size and statistical analysis

Our trial aims to demonstrate that LLND could decrease the 3-year local recurrence rate of low rectal cancer patients with suspicion of LLN metastases. Based on previous studies, we assume that the 3-year local recurrence rate for patients with suspicion of LLN metastases who do not undergo LLND is 15% [13–16], and LLND is expected to show a reduction of 7 percentage points. G*Power 3.1 is used to calculate the sample size. A statistical power of 0.80 and a significance level of 0.05 are chosen, and we assume that there will be a 10% dropout rate. Therefore, 512 patients are needed in this specific trial (256 patients in each group).

All participants in this trial will be analyzed using the intention-to-treat analysis. The chi-square test and Student’ *t* test will be used to compare categorical data and continuous data for the two groups, respectively. The 3-year local recurrence rate, the primary endpoint of this trial, will be analyzed using the Kaplan-Meier method, as well as OS and DFS. In addition, based on different characteristics (such as age, sex, tumor stages, etc.), which can identify the influence of competing risk factors, the Cox proportional hazards (PH) regression model will be tested if Schoenfeld Residuals Analysis confirms PH assumption validation. Otherwise, an alternative extended Cox PH model will be used. SPSS 21.0 (SPSS Inc., Chicago, IL, USA) will be used for all statistical analyses, and a *P* value < 0.05 is considered significant.

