## Discussion

Currently, the hot issue of the treatment of LLN in advanced rectal cancer patients is still being debated in different regions. Eastern countries, especially Japan, favor LLND following TME; however, Western countries believe that nCRT and TME is recommended, and LLDN is added only when a LLN is preoperatively diagnosed as metastatic. Actually, preoperatively enlarged LLNs are not common and only a small proportion of LLDs with a maximum short-axis diameter ≥10 mm, or with a spiculated or indistinct border, or a mottled heterogenic pattern are diagnosed as metastatic [23]. The remaining large proportion of LLNs are underdiagnosed as being metastatic and often confuse surgeons’ treatment strategy. Thus, our trial pays particular attention to this stratification of suspicious LLNs, assessing the efficacy and safety of the LLND in advanced rectal cancer patients.

Another issue we have considered in our trial is the randomization time. In our trial, we randomly allocated participants before nCRT rather than after nCRT. Because LLN metastases are commonly diagnosed before nCRT by their features on pelvic MRI or CT and when chemo-radiation has achieved its effect, the treatment-sensitive regions of any enlarged LLNs will have decreased in size which may confuse the randomization if allocation is performed after nCRT.

This trial is the first randomized controlled trial to investigate the role of LLND in reducing local recurrence rates for low advanced rectal cancer patients with suspicion of LLN metastases. If the efficacy of LLND is verified, which reduces the local recurrence rate from 15% to 8%, LLND can be recommended as a new standard strategy for low advanced rectal cancer patients with suspicion of LLN metastases.

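### Table 1 makes surgical results part of eligibility although patients are randomised before nCRT, so applying it as written can remove randomised patients with allocation known

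*Protocol article*

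**What the plan says.** **Timing.** The Discussion states that "we randomly allocated participants before nCRT rather than after nCRT". The Intervention section gives the same order: randomisation, one chemotherapy cycle, radiotherapy, three further cycles, then surgery about 3 to 4 weeks later.

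**Eligibility.** Under Study population, the inclusion half of Table 1 lists "Mesorectal excision is performed", a group of operative findings that includes "Lower tumor margin is below the peritoneal reflection", and "Stage R0 after resection". In the exclusion half, the criterion for confirmed lateral node metastasis contains the condition "after nCRT has been completed, lymph node enlarges more than 30" per cent. The text above the table says that eligible patients comply strictly with the criteria.

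**Allocation.** The section Randomization and blinding says: "All eligible participants meeting the inclusion criteria will be randomly allocated into either the TME + LLND group or the TME group". It also leaves participants, surgeon and investigators aware of the assignment.

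**Analysis.** The section Sample size and statistical analysis says: "All participants in this trial will be analyzed using the intention-to-treat analysis".

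**The concern.** An eligibility criterion should be decidable when the patient is randomised. Whether the excision was done and whether the margins were clear are learned after the whole neoadjuvant course and the operation. If these items are enforced as eligibility, they act as exclusions after randomisation, applied by people who know the arm.

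Patients who are not resected or not R0 are plausibly at higher risk of local recurrence, which is the outcome that the sample size rests on. R0 status and performed excision are also results of the surgery, and the surgery is what the trial compares. If such patients are removed, the groups analysed are no longer the groups randomised, and the losses need not be equal. That would undo the protection that the intention-to-treat rule is meant to give.

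**Working it through.** **Step 1. When each item can be known.** Randomisation comes before nCRT.

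| Table 1 item | Earliest time known | Can allocation affect it? |
|---|---|---|
| Mesorectal excision performed | Surgery | Possibly; the operation differs by arm |
| R0 resection | Surgery and pathology | Possibly; the operation differs by arm |
| Tumour level as an operative finding | Surgery, though imaging may judge it earlier | No; only its assessment could differ |
| Node growth after nCRT | Scan after nCRT | No; both arms receive the same nCRT, so only its assessment could differ |

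The first two items cannot be met before allocation. For them, the rule that patients meet the inclusion criteria and are then randomised is impossible.

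**Step 2. The node-growth clause.** It is joined by *and* to a short-axis diameter above 10 mm. The inclusion criteria already require extramesorectal nodes below 10 mm. If both sizes are measured at baseline, the clause could remove no eligible patient. It acts only if size is reassessed after nCRT or if *and* is meant as *or*. The text does not say which.

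**Step 3. Illustration with a true difference that exclusion hides.** The article gives no R0 rates, so every rate here is an assumption. Let local recurrence be 12% in R0 patients of both arms and r in non-R0 patients, with non-R0 proportions a and b in the two arms.

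- All randomised patients: rate = (1 − a) × 0.12 + a × r, and the same with b. Difference = (a − b) × (r − 0.12).
- R0 patients only: difference = 0.12 − 0.12 = 0.

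| Non-R0, a vs b | r | Calculation | Shift caused by exclusion |
|---|---|---|---|
| 8% vs 4% | 30% | 0.04 × 0.18 | 0.7 points |
| 8% vs 4% | 50% | 0.04 × 0.38 | 1.5 points |
| 10% vs 5% | 30% | 0.05 × 0.18 | 0.9 points |
| 10% vs 5% | 50% | 0.05 × 0.38 | 1.9 points |

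The planned effect is 15% − 8% = 7 points, so the largest shift is 1.9 / 7, or about 27% of it.

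**Step 4. Illustration with no true difference.** Let overall recurrence be 15% in both arms. A fraction e of an arm is excluded and recurs at rate r. The rate in those kept is (0.15 − e × r) / (1 − e).

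- Exclusion 5% vs 5%: the same rate in both arms for any common r, so the spurious difference is 0.
- Exclusion 5% vs 10%, r = 30%: 0.135 / 0.95 = 14.2% against 0.120 / 0.90 = 13.3%, a spurious 0.9 points.
- Exclusion 5% vs 10%, r = 50%: 0.125 / 0.95 = 13.2% against 0.100 / 0.90 = 11.1%, a spurious 2.0 points (0.1316 − 0.1111 = 0.0205).

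Take 230 per group before exclusion (256 × 0.9, after the stated 10% dropout) and a two-sided normal test at 5%. The type I error in the two unequal cases is then about 6% and 10%.

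Steps 3 and 4 work through different mechanisms. In step 3 exclusion hides a difference, and in step 4 it creates one. The results depend on the assumed imbalance, and neither step fixes a direction.

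**The case against.** A reader might infer that the plan intends to drop non-R0 or unresected patients, or that Table 1 and intention-to-treat cannot both be followed. The article does not go that far. No section says that such patients leave the analysis. The Dropping out section gives six reasons, and none names failed R0, no excision, tumour level or node growth. One can read the article as keeping everyone in the analysis, with the criteria merely misplaced. This part of the objection stands: the text permits exclusion but does not show that it is planned. The demand for strict compliance and the undefined term *participants* leave the matter open.

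A reader might also infer that all these exclusions depend on the arm. That fits the surgical results only. Even for R0, both arms have standard TME, and nothing in the article shows that LLND changes the R0 rate. Nor can the node-growth clause be treated as a clear exclusion after randomisation, for the reason in step 2.

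Finally, an article condenses a full protocol, and analysis sets are commonly left to the SAP, which is not shown. That answers a complaint about missing detail. It does not answer this point, which is that printed criteria conflict with the printed time of randomisation. The article describes no second registration at surgery that would resolve the conflict.

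**Conclusion.** The ordering conflict is established from the article alone: criteria that depend on surgery stand as inclusion criteria for patients randomised before nCRT. Applying Table 1 literally can remove randomised patients with allocation known, contrary to the stated intention-to-treat analysis. For R0 status and performed excision, balance between arms cannot be assumed.

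That bias will occur, or that it would favour one arm, is not established. The calculated shifts rest wholly on assumed non-R0 rates, assumed recurrence in those patients and an assumed imbalance. They show only that the effect could matter against the planned difference. The contradiction should still be resolved, because it concerns who is counted in the primary comparison.

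**What to change.** 1. In Table 1, define eligibility only by items known before randomisation, such as histology, clinical stage, imaging before nCRT and performance status.
2. Move performed excision, operative findings, R0 status and node growth after nCRT out of eligibility. Record them as post-randomisation data and use them only to define a secondary per-protocol set. If the node-growth clause is kept in any role, state its *and*/*or* logic and when size is measured.
3. State that the primary set is every randomised patient in the allocated arm, including those not resected or not R0.
4. Define a time origin that serves patients who are never operated on. The Outcomes section starts DFS and OS at surgery, so they have none at present.
5. Reconcile Study population, Randomization and blinding, Intervention, Sample size and statistical analysis, and Discussion. How such patients are managed clinically is for the protocol to reconcile and is not addressed here.

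The cost is a protocol amendment and matching SAP wording. Keeping patients who could not benefit from LLND may dilute the effect slightly. The article says that the trial is already enrolling, so any randomised patient already removed on these grounds should be identified and restored to the primary set. Rewording alone does not recover follow-up that was not collected.

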### Randomization and blinding

All eligible participants meeting the inclusion criteria will be randomly allocated into either the TME + LLND group or the TME group. Based on one previous study, randomization is performed using a computer-generated, blocked randomization sequence with a block size of 4 at a 1:1 ratio [19]. The patients will be informed about the treatment details upon admission the day before surgery. Owing to the specificity and ethics, this trial allows the participants, the surgeon, and the investigators to be aware of the whole assignment.

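### Allocation precedes months of identical neoadjuvant treatment and may be known to surgeon and investigators throughout, so exclusions and withdrawals before surgery could depend on the arm

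*Protocol article*

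**What the plan says.** **Timing of randomisation.** The Discussion states: "In our trial, we randomly allocated participants before nCRT rather than after nCRT". Its reason is that enlarged nodes shrink under treatment, which could confuse a later allocation.

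**Pathway after randomisation (Intervention).** It starts the same way for everyone: "After randomization, all participants will firstly receive a cycle of 5-fluorouracil with oxaliplatin therapy (FOLFOX) or capecitabine (Xeloda) with oxaliplatin therapy (XELOX"). Then "radiotherapy with 50.4 Gy is administered in 28 separate doses", then "three cycles of FOLFOX or XELOX will be continued". The arms separate only at the operation: "About 3 to 4 weeks later, patients allocated to the TME group will undergo standard TME surgery solely", while the other arm has LLND added. No rule is given for choosing between the two regimens, and adjuvant chemotherapy follows whichever was used before surgery.

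**Who knows the arm (Randomization and blinding).** Two adjacent sentences apply. One reads "The patients will be informed about the treatment details upon admission the day before surgery". The next, citing the nature of the trial and ethics, says that "this trial allows the participants, the surgeon, and the investigators to be aware of the whole assignment". The Study design section nevertheless says: "This is a prospective, multicenter, randomized controlled, single-blinded, phase III trial". The Abstract uses the same label. No blinded role is named.

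**Decisions that can fall between randomisation and surgery.** In Table 1, the exclusion for confirmed lateral node metastasis includes node growth of more than 30% once nCRT is complete. The table also allows exclusion at the physician's discretion, with no time limit. The Dropping out section lets an investigator withdraw a patient for the patient's benefit and lists poor compliance as a ground.

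**Analysis.** The Outcomes section counts disease-free survival (DFS) and overall survival (OS) from surgery. The statistical section promises an intention-to-treat analysis of all participants.

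**The concern.** A surgeon cannot be blind to the operation being performed. That explains open allocation in theatre, but not in the months before it, when treatment is the same in both arms and nobody delivering it needs to know the arm. The Discussion defends early randomisation but does not address early knowledge of the result.

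What is at stake is mainly selection. A clinician who knows that suspicious nodes will be left in place, or will be dissected, may read a borderline change in node size differently, or be readier to exclude or withdraw the patient. If such losses differ between arms in number or in type of patient, the groups that reach surgery are no longer those that randomisation created. The comparison would then not isolate the effect of LLND.

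**Working it through.** **1. Length of the window.** The article gives no figure for the time from randomisation to surgery, so there is none to reproduce. From the Intervention section: 1 cycle, 28 fractions, 3 cycles, then 3 to 4 weeks. Assumptions not in the article: a 2-week FOLFOX cycle, a 3-week XELOX cycle, 5 fractions a week and no breaks between blocks.

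Weeks = c + 28/5 + 3c + gap, where c is the cycle length.

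- FOLFOX: 2 + 5.6 + 6 + (3 to 4) = 16.6 to 17.6 weeks
- XELOX: 3 + 5.6 + 9 + (3 to 4) = 20.6 to 21.6 weeks

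The range is about 17 to 22 weeks (3.8 to 5.0 months at 4.345 weeks per month). This is the interval from randomisation to surgery. It is also the period of open knowledge only if the allocation is released to staff at randomisation.

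**2. Decisions inside the window.**

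- *Regimen choice:* made after randomisation, with no stated rule.
- *Node growth after nCRT:* can only be judged after randomisation, and implies a restaging read by staff who may know the arm.
- *Discretionary exclusion:* no time limit stated.
- *Withdrawal by the investigator or for poor compliance:* allowed once the trial has begun.

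**3. Does intention-to-treat close the gap?** Not clearly. A patient lost before the operation has no starting point for DFS or OS as defined. The article gives no separate time origin for local recurrence, but the trial also requires an R0 resection. Promising to analyse all participants while starting the clock at surgery leaves unclear how these patients enter either primary outcome.

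**4. How large could selective loss be?** This is an illustration only. Take no true effect and the article's control rate p = 15% in both arms. Let an extra share d of one arm be lost from the analysis, with recurrence risk r. Both d and r are assumptions.

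Observed rate in that arm = (p − d·r) / (1 − d)

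| d | r | Observed rate | Shift (points) |
|---|---|---|---|
| 5% | 25% | (0.15 − 0.0125)/0.95 = 14.5% | −0.5 |
| 5% | 30% | (0.15 − 0.015)/0.95 = 14.2% | −0.8 |
| 10% | 25% | (0.15 − 0.025)/0.90 = 13.9% | −1.1 |
| 10% | 30% | (0.15 − 0.03)/0.90 = 13.3% | −1.7 |
| 10% | 15% | (0.15 − 0.015)/0.90 = 15.0% | 0.0 |
| 10% | 8% | (0.15 − 0.008)/0.90 = 15.8% | +0.8 |

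The planned difference is 15% − 8% = 7 points. The shift arises only if the patients lost differ in risk from those kept. Its direction depends on which arm loses them.

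**5. Patients.** Being told the day before surgery and being allowed to know the assignment throughout cannot both govern the nCRT period. If participants, surgeon and investigators may all know, it is also unclear who the single-blinded label covers.

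**The case against.** **The start of the window is inferred.** The article says who may know, not from when. The only disclosure time it gives is the day before surgery, and release timing is a detail that an article may leave to the full protocol. This stands as a limit on certainty: the 17 to 22 weeks is conditional. But the point does not rest on an omission. The article grants surgeon and investigators access without restriction, and ties staged disclosure to patients alone.

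**Patients.** A reader might infer that patients know their arm for months and can leave because of it. The text does not support this. One of its two sentences puts disclosure the day before surgery, and on that reading patient-led withdrawal during nCRT cannot depend on the arm. What remains is the contradiction.

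**Radiotherapy.** A reader might also infer that undissected nodes could be irradiated more intensively. Dose and number of fractions are fixed for all participants, so that would be a protocol deviation and not discretion that the plan allows. It is not part of the case.

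**Chemotherapy.** Both regimens are open to both arms, with the same number of pre-operative cycles and the same total of eight. Nothing in the article shows that the choice affects local recurrence. This is fair: regimen choice is a weaker route than exclusion and withdrawal.

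**Common standards.** The Data collection section describes uniform criteria and nCRT standards across centres, managed by a research company. That should limit variation between sites. It does not stop someone who knows the arm from making a discretionary exclusion or withdrawal.

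**Conclusion.** The concern holds for surgeon and investigators, on the condition that allocation reaches them at or soon after randomisation. They could then know the arm for about 17 to 22 weeks of identical treatment while making decisions that determine who reaches surgery. With follow-up starting at surgery, the intention-to-treat statement does not clearly protect either primary outcome. Under the assumed inputs, selective loss of 5 to 10% of one arm at 25 to 30% risk would create a difference of 0.5 to 1.7 points. That is not trivial against 7 points, but it would not account for the planned effect.

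For patients, the finding is only that the article's statements conflict and must be reconciled.

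Two stronger readings should be resisted. The article shows that arm-dependent loss can arise, not that it has. A reader might also infer that the effect would be diluted: if 5 to 10% of the LLND arm did not receive LLND, 15% − [8%(1 − q) + 15%q] gives 6.65 points at q = 5% and 6.30 at q = 10%. The arithmetic is right, but it measures an assumed crossover rate that later disclosure would not necessarily prevent, so it is no support for this point.

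**What to change.** Keep randomisation before nCRT, and change when the result is released:

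1. Record the choice of FOLFOX or XELOX before randomisation.
2. Withhold the allocation from investigators, surgeon and patient until pre-operative treatment, the restaging read and any post-nCRT exclusion or withdrawal decision are recorded. Then release it in the pre-operative period, building on the disclosure point already used for patients.
3. Limit the open-assignment sentence to the time after release. Reconcile it with the sentence on informing patients and with the single-blinded label.
4. Log each pre-operative exclusion or withdrawal as before or after release.

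**Cost.** No extra patients, visits or procedures are needed. Theatre time for LLND is booked later or provisionally, and the allocation list must be held away from the sites. The article reports that enrolment is under way, so only patients randomised after the amendment benefit, and results before and after it should be identifiable. The change does not reach the R0 criterion, which is judged after the operation.
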